### Process evaluation: qualitative interviews

A process evaluation, informed by the RE-AIM^20^ framework, will be conducted to better understand the views and experiences of clinicians and patients regarding the two treatment paths in the trial. This information would be useful regardless of the trial result, allowing a better understanding of trial outcomes and assisting in identifying potential barriers and facilitators to future implementation. RE-AIM considers the target population (*Reach* (eg, representativeness), *Effectiveness* of the service, whether clinicians, patients and key stakeholders are willing to *Adopt* the service, fidelity (eg, clinician and patient adherence), barriers and facilitators to *Implementation* and the extent to which the service can become part of practice or policy (Maintenance)). RE-AIM will use quantitative data sources (eg, health resource use, patient adherence to the intervention and clinician fidelity to the protocol) and qualitative data sources (eg, interviews with physiotherapists, patients and key stakeholders). A more detailed outline of the process evaluation will be published a priori. All qualitative aspects of this study will be reported according to the consolidated criteria for reporting qualitative research (COREQ).^21^

We will attempt to interview 10 physiotherapists involved in delivering the physiotherapist-led triage and treatment service, 20 participants from the usual care group and 20 from the physiotherapist-led triage and treatment service (with a similar number of participants from the three treatment subgroups). The anticipated sample size was informed by the concept of information power that considers the study aim, specificity, theory, dialogue and analysis to guide planning for sample size in qualitative research.^22^ The actual sample size may vary based on the saturation of elicited themes. We will attempt to purposively sample physiotherapists involved in delivering the physiotherapist-led rapid triage phone service by age, gender, familiarity with telehealth and years of experience. We will attempt to purposively sample patient participants to achieve diversity in presenting musculoskeletal condition, age, gender, ethnicity, trial arm, treatment subgroup (if in the intervention group) and response to the intervention.

To gain an in-depth understanding of potential barriers to broader implementation, we will also aim to interview 10 physiotherapists who may be interested in this new model of care but were not involved in the trial, 10 patients who dropped out of this trial or chose to not participate, 10 patients who did not attend their appointments and 10 key stakeholders (n=10) (eg, heads of allied health, physiotherapy departments at hospital sites in NSW, representatives from Sydney Health Partners and government-funded insurance authorities), with the anticipated sample size calculated as per earlier.

An experienced researcher and physiotherapist will conduct all qualitative interviews. The role of the interviewer as an active participant in the research process will be critically acknowledged through reflexivity. The interviewer will take field notes to document personal assumptions and biases, and the research team will critically evaluate how their interactions with participants may be shaped by their prior experiences and beliefs through regular reflective practice and peer debriefing.

In this study, the assumed research paradigm is pragmatism as our trial focuses on evaluating the practicality and effectiveness of a physiotherapist-led triage and treatment service in Australian public health physiotherapy clinics. This approach will allow us to make a practice, actionable critique of our new model of care, drawing on the experiences of patients, their health professionals and other key stakeholders.^23^ The paradigm is appropriate for person-centred research as it focuses on applying different research methods, forms and value hierarchies to gain knowledge, asserting that optimal definitions for social problems emanate from the people experiencing them.^23^

### Blinding

Therapists and assessors will not be blinded. The surveys administered during this trial are self-assessments completed by participants who will be blind to the study hypothesis (ie, will not be aware of what the new model of care involves). Blinding participants to the study hypothesis will be achieved by providing participant information sheets that do not mention the study hypothesis and state that the study is comparing two models of care (without specifying which model is the intervention of interest).

### Statistical methods

A detailed Statistical Analysis Plan and Health Economics Analysis Plan (HEAP) including mock tables will be developed before unblinding and shared with the Data Monitoring and Safety Board (DMSB). Prespecified analyses will be programmed using randomly scrambled treatment allocations. Unblinded results will be presented to the study team once all analyses have been programmed and validated.

### Primary analysis

The purpose of our trial is to assess whether the physiotherapist-led triage and treatment service is as good as or better than usual clinic-based care for improving function and better than usual care in terms of reducing treatment waiting time. The between-arm difference in PSFS scores at 6 months postrandomisation is a coprimary outcome and we have prospectively defined a noninferiority margin of −0.7 points for this analysis. This is the maximal compromise on the outcome we are prepared to tolerate (based on guidelines^18^ and consumer feedback) and still consider the physiotherapist-led triage and treatment service to be clinically noninferior to usual clinic-based care. We will test the null hypothesis that the mean difference in PSFS scores (intervention − usual care) is no greater than −0.7 (H0: mean difference ≤−0.7). To declare noninferiority for the new model of care when compared with usual clinic-based care, the 95% CI around the mean difference should be entirely above the noninferiority margin, that is, the lower bound of the 95% CI must be higher than −0.7. A repeated-measure linear mixed model including all postrandomisation PSFS measurements will be used to generate an adjusted mean difference and 95% CI representing the comparison of PSFS scores between the intervention and usual care arms at each time point. The model will be adjusted for the baseline PSFS value (to improve statistical precision), hospital site and treatment subgroup allocation.

The between-arm difference in treatment waiting time is the other coprimary outcome, provided the physiotherapist-led triage and treatment service is as good or better than usual clinic-based care for improving function (hierarchical approach). We have prospectively defined an effect size of 14 days or greater to be clinically important (approximately half the reduction found in the PhysioDirect trial).^8^ This is the difference that our consumers and clinician partners consider meaningful. A generalised linear model will be used to generate an adjusted mean difference and 95% CI representing the comparison of treatment waiting times between the intervention and usual care groups. The model will be adjusted for hospital site and treatment subgroup allocation.

Imputation techniques may be considered if more than 5% of any outcome data are missing, depending on patterns within missing data.

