### Outcomes

The coprimary outcomes are physical function as assessed by the Patient Specific Functional Scale (PSFS) at 6 months postrandomisation and treatment waiting time (from randomisation to first treatment). PSFS scores at 3 and 12 months are secondary outcomes. Participants completing the PSFS list up to five functional tasks currently limited by their musculoskeletal condition and score each task based on their current level of ability—0 (unable to perform activity) to 10 (able to perform activity at the same level as before the complaint). Scores for each activity will be summed and calculated as an average of the total possible score for the participants (determined by the number of identified activities). This generic measure will be used as patients with a wide range of musculoskeletal pain presentations will be included in the trial, and it compares well with disease-specific measures in terms of reliability and validity.^10 12 13^ Treatment waiting time will be assessed as the number of days from randomisation to the first appointment with a physiotherapist (either telephone, video conference or clinic-based). It will also be expressed as the number of days from the referral date to the first appointment with a physiotherapist to understand treatment waiting times across sites before, during and at the end of the trial recruitment period; this will be a secondary outcome.

Secondary outcomes (eg, pain and quality of life), health resource measures (eg, number of clinic-based appointments and number of telehealth appointments), potential mediators (eg, pain self-efficacy and recovery expectations), process measures (eg, adherence and usability of PT eXercises App) and adverse events are outlined in online supplemental appendix 3.

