### Sample size

A total sample of 368 participants will provide 90% power to exclude a noninferiority margin of 0.7 points on the 11-point PSFS with a 15% loss to follow-up,^8^ an SD of 1.9, two-sided α of 5% and PSFS at 6 months in the control arm participants of 5.8—based on a recent trial conducted in the same setting.^14^ A between-group difference of ≤0.7 points will indicate that the new physiotherapy model of care is noninferior (as good as or better) compared with usual clinic-based care. We chose an SD of 1.9 as it is between the mean value of the SD for the PSFS at follow-up in published studies of similar patient populations with the SDs of 1.7,^15^ 2.0^12^ and 2.1^16^. The minimal important difference (MID) for the PSFS ranges from 1.3 (small change) to 2.7 (large change).^17^ Guidelines suggest using a noninferiority margin of 50% (or less preferably) of the expected treatment effect.^18^ Thus, we chose a conservative between-group noninferior margin of 0.7 (50% of the MID of 1.3).

If our physiotherapist-led triage and treatment service is noninferior for improving function at 6 months compared with usual care, we will interpret the findings for treatment waiting time as a coprimary outcome. This hierarchical approach to our coprimary outcomes was selected because consumer feedback suggested that reducing waiting times is not valuable if patient outcomes are adversely affected. Our sample size of 368 participants will provide >80% power to determine a conservative 14-day mean reduction in waiting time (approximately half of the reduction found in the PhysioDirect trial^8^), calculated from medians and interquartile ranges with this formula,^19^ using an SD of 43 (conservative SD from participating public hospital outpatient clinics over the past 5 years), two-sided α of 5% and 15% loss to follow-up.

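### The coprimary waiting time is a mean number of days to a first appointment not defined as booked or attended, with no rule for participants who are never seen

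*Protocol article*

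**What the plan says.** The Outcomes section names the coprimary outcome as "treatment waiting time (from randomisation to first treatment", and the abstract describes it the same way. The Outcomes section then makes it operational: "Treatment waiting time will be assessed as the number of days from randomisation to the first appointment with a physiotherapist", by telephone, video or in clinic. It does not say whether the appointment must have been attended.

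The Primary analysis section fixes the model and the effect measure: "A generalised linear model will be used to generate an adjusted mean difference and 95% CI representing the comparison of treatment waiting times", adjusted for hospital site and treatment subgroup. A difference of 14 days or more is defined as clinically important. The only text on absent values is "Imputation techniques may be considered if more than 5% of any outcome data are missing, depending on patterns within missing data".

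The Sample size section states: "Our sample size of 368 participants will provide >80% power to determine a conservative 14-day mean reduction in waiting time". It does so "using an SD of 43 (conservative SD from participating public hospital outpatient clinics over the past 5 years", with a two-sided 5% level and 15% loss to follow-up. The process evaluation plans to interview "10 patients who did not attend their appointments", along with patients who dropped out or declined.

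Table 1 describes how first contact happens. Low-risk intervention participants are advised during the call that tells them their allocation. Medium-risk and postoperative intervention participants have a telehealth appointment booked in that call, and high-risk intervention participants a clinic appointment. Usual-care participants also have a clinic appointment booked in the call, at the usual clinic wait.

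**The concern.** Time to first treatment is an event time, and some participants may never have the event. A model for mean days needs a number for each participant. If the appointment must be attended, people never seen either leave the analysis or are given an imputed date. Imputing a functional score estimates a value that exists but was not recorded. Imputing a first-treatment date for someone never treated has no such target.

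Dropping them is safe only if being seen is unrelated to arm and to the length of the wait. Table 1 gives reason to doubt this. A low-risk intervention participant who takes the allocation call has been seen and has no later first appointment to miss. A usual-care participant has the whole clinic wait in which to recover, go elsewhere or not attend. Attendance happens after randomisation and may be linked to the quantity being measured, and adjusting for site and subgroup does not remove that link.

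At stake is one of two coprimary results, read against a 14-day threshold that is also the difference the trial is powered to detect.

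**Working it through.** **1. The protocol's own power figure.** Inputs from the Sample size section: 184 per arm, 15% loss, difference 14 days, SD 43, two-sided 5%.

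- Per arm after loss: 184 × 0.85 = 156.4.
- Standard error: 43 × √(2/156.4) = 4.86 days.
- Power: Φ(14/4.86 − 1.96) = Φ(0.92) = 82.1%.

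The stated figure of more than 80% reproduces, so the sample size is not in error. The calculation allows 15% of waiting-time values to be absent.

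**2. Who has a value under each reading.**

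| Participant | Booked date | Attended date |
|---|---|---|
| Intervention, low risk, reached by the call | date of the call | date of the call |
| Intervention, medium risk, postoperative or high risk | exists once booked in the call | only if attended |
| Usual care | exists once booked in the call | only if attended |

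The undefined word decides who is in the analysis. On the booked reading almost everyone has a value, but it is not time to first treatment for those who do not attend. On the attended reading the outcome matches its stated meaning, but never-seen participants have no value.

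**3. Possible size on the attended reading.** The documents give no mean wait and no attendance rate, so everything in this step is assumed apart from the SD of 43 and the 14 days.

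*Gamma waits.* Control mean μ of 34, 40 or 48 days with SD 43; intervention mean 14 days lower, with its SD scaled in proportion. The probability of attending is 0.95·exp(−h × wait), with h from 0.001 to 0.004 per day. Among attenders the mean is μ/(1 + hθ), where θ = SD²/μ; the 0.95 cancels.

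Worked case, means 40 and 26, h = 0.004:

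- Control: θ = 43²/40 = 46.2; 40/(1 + 0.185) = 33.8 days.
- Intervention: θ = 46.2 × 26/40 = 30.0; 26/(1 + 0.120) = 23.2 days.
- Observed difference: 10.6 days (10.55 before rounding).

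| Means (control, intervention) | h = 0.001 | h = 0.004 | h = 0.004, loss in controls only |
|---|---|---|---|
| 48, 34 | 13.1 | 10.9 | 7.6 |
| 40, 26 | 13.0 | 10.6 | 7.8 |
| 34, 20 | 12.9 | 10.2 | 7.9 |

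With both arms affected, non-attendance is about 8–21% in controls and 7–16% in the intervention arm.

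*Lognormal waits.* Control mean 45, 60 or 90 days, SD 43, 15% control non-attendance, log-odds of non-attendance rising by 0.01 or 0.02 per day. Simulation gives a control mean among attenders that is about 3 to 7 days too short. The between-arm difference is about 10 to 14 days if the same relation holds in both arms, and about 7 to 11 days if all loss is in controls.

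**The case against.** The strongest objection is that the first appointment may simply mean the booked one. It is arranged in the allocation call for both arms, so nearly everyone would have a value and nothing would condition on attendance. The text allows this reading. It does not settle the matter, because the abstract and the Outcomes section both speak of first treatment.

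The evidence for non-attendance is indirect. The interview group is a quota, is not limited to first appointments, and gives no rate and no arm. The 15% is loss to follow-up, the same figure as for physical function. A reader might infer that 15% will never attend, but the protocol does not say so.

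A reader might also infer that attendance is known to differ by arm, or that the bias must work against the new service. Neither is documented. Both arms depend on being reached by the same call, many intervention participants also have an appointment to miss, and missed telehealth bookings could push the other way.

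A time-to-event analysis has its own distortion. As an assumed example, suppose treated controls wait 45 days on average with 15% never treated, and treated intervention participants wait 31 days with 5% never treated. Counting the never-treated as waiting to day 180 gives 0.85 × 45 + 0.15 × 180 = 65.25 against 0.95 × 31 + 0.05 × 180 = 38.45. That is a difference of 26.8 days, of which 12.8 come from non-attendance. The Introduction also cites waits of up to 12 months, which a 180-day horizon would cut off. This stands, and it shapes the fix.

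Finally, a detailed analysis plan is promised and may define a rule for never-seen participants. That is a fair reason not to fault missing detail. But the model and effect measure are already fixed in the protocol, for an outcome that may be undefined for some participants. Nor is the alternative mere taste: the Introduction reports the earlier UK trial's waiting result as medians and a time ratio.

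**Conclusion.** The point holds as a defect of definition and analysis for a coprimary outcome. The protocol does not say whether the appointment is booked or attended. On the attended reading its mean-days model has no value for people never seen, and the only fallback is optional imputation of a date that does not exist. Because first contact is arranged differently by arm, a mean among attenders may not compare the groups as randomised.

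The direction and size of any bias are unknown. If non-attendance rises with waiting time alike in both arms, a true 14-day difference would appear as about 10 to 14 days. If all loss is in controls, the lower end is about 7 days. These figures rest on assumed distributions, means and attendance relations. A reader might take the 3 to 7 days in the lognormal illustration as the bias in the trial result. It is the shift in the control mean only, and it carries over in full only if the intervention arm is unaffected. The stated power is correct.

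**What to change.** - State that the event is the first attended contact with a physiotherapist, by any mode.
- Analyse all randomised participants with a time-to-event method adjusted for site and subgroup and reported in days, for example the difference in restricted mean time to first treatment, so that the 14-day benchmark stays usable.
- Prespecify a horizon long enough for the waits expected at the sites.
- Keep never-seen participants in the analysis, with a stated rule for those who cancel because they recovered or went elsewhere, and report the proportion never treated by arm.
- As sensitivity analyses, give the generalised linear model in attenders and an analysis of the booked first-appointment date (date of the call for low-risk intervention participants).
- Do not impute first-treatment dates for people never treated.

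The cost is wording in the analysis plan and standard software. Power need not suffer. With exponential waits at the three pairs of means in the gamma table (rate ratios 1.41 to 1.70) and 313 first treatments (85% of 368), Φ(√(313/4) × ln(ratio) − 1.96) gives 86% to 99.7%. That formula is for a rate-ratio test and is only a guide for a restricted mean. The downside is that the estimate depends on the horizon and partly reflects non-attendance, which is why the sensitivity analyses are needed.

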### Secondary analysis

Similar linear models will be used to analyse between-group differences in other continuous outcomes, while logistic regression will be used to estimate the treatment effect for binary outcomes. All analyses of secondary outcomes will be adjusted for baseline values (if applicable), hospital site and treatment subgroup allocation as per the primary analysis.

### Cost-effectiveness analysis

Costs will be measured using a combination of trial records, administratively linked data, healthcare diaries and published data: healthcare costs (based on local costing models) and intervention costs (clinician time and wage, and other resources required to deliver the interventions). Comparisons made between the new model of care and usual care arms will be generated through the economic evaluation which will estimate the difference in the cost and benefits between the arms of the trial. The economic assessment method will adhere to best practice guidelines for economic evaluations alongside noninferiority trials.^24^

Wherever possible, the costs will be standardised to current prices. Quality-adjusted life-years (QALYs) will be generated through the utilisation of the EuroQolEQ-5D-5L questionnaire outcomes which will be compared with the national Australian value set.^25^ To avoid biases associated with complete case analysis, multiple imputation methods may be employed to impute missing data as described in more detail in the HEAP. Incremental cost per QALY gained will demonstrate the results of the economic evaluation.

Predefined equivalence margins for costs and QALYs will be chosen as recommended by guidelines.^24^ Incremental costs and QALYs will be calculated in terms of the difference between those in the physiotherapist-led triage and treatment service group and the usual care group. Bootstrapping will be used to estimate a distribution around costs and QALYs and will be plotted on a cost-effectiveness plane. The cost-effectiveness plane and the predefined equivalence margins will be used to determine the probability of the physiotherapist-led triage and treatment service being noninferior to usual care. One-way sensitivity analyses will be conducted around key cost variables, and a probabilistic sensitivity analysis will be conducted to estimate the uncertainty in all parameters.

### Qualitative interview analysis

All interview data will be analysed using thematic analysis, a method for identifying, analysing and reporting patterns within qualitative data.^26^ We will employ the Braun and Clarke six-step framework for thematic analysis, which includes familiarisation with the data (Step 1), generating initial codes (Step 2), searching for themes (Step 3), reviewing themes (Step 4), defining and naming themes (Step 5) and producing the report (Step 6).^27^ In practice, two researchers will independently familiarise themselves with the interviews (via audio-recording or transcribed interviews using the Otter AI software), record initial observations and identify concepts relevant to the questions asked. The two researchers will then organise concepts into broader themes and subthemes in NVivo that will be discussed with the other co-investigators. Any disagreements in categorising concepts into themes and subthemes will be discussed and resolved. The mapping of themes and subthemes will be iterative as new data emerges. Interview themes and subthemes will be matched to the appropriate five dimensions of the RE-AIM^20^ framework (Reach, Effectiveness, Adoption, Implementation and Maintenance) to further understand contextual factors. Interviews will stop after three consecutive interviews where no new themes have emerged (data saturation).

